# Cognitive behaviour therapy for non-cardiac pain in the chest (COPIC): a multicentre randomized controlled trial with economic evaluation

**DOI:** 10.1186/s40359-015-0099-7

**Published:** 2015-11-24

**Keywords:** Cognitive behaviour therapy, Non-cardiac chest pain, Randomized trial

## Abstract

**Background:**

Most patients with chest pain have nothing wrong with their cardiac function. Psychological forms of treatment for this condition are more likely to be successful than others.

**Methods/design:**

A two-arm parallel controlled randomized trial of standard care versus a modified form of cognitive behaviour therapy for chest pain (CBT-CP) in patients who have attended emergency hospital services. Inclusion criteria include (i) emergency attendance more than once in the previous year with chest pain when no physical pathology has been found, (ii) aged between 16 and 75, (iii) signed consent to take part in the study. Exclusion criteria are (i) under current psychiatric care, (ii) those who have had new psychotropic drugs prescribed within the last two months, (iii) are receiving or about to receive a formal psychological treatment. Those satisfying these criteria will be randomized to 4–10 sessions of CBT-CP or to continue with standard care.

Participants are randomized using a remote web-based system using permuted stacked blocks stratified by study centre. Assessment is carried out at baseline by researchers subsequently masked to allocation and at 6 months and 1 year after randomization. The primary outcome is the Health Anxiety Inventory score at 6 months, and secondary outcomes are generalised anxiety and depressive symptoms, the Lucock Health Anxiety Questionnaire adapted for chest pain, visual analogue scales for chest pain and discomfort (Inskip Scale), the Schedule for Evaluating Persistent Symptoms (SEPS), health related quality of life, social functioning and medical resource usage. Intention to treat analyses will be carried out with clinical and functioning data, and a cost-utility analysis will compare differences in total costs and differences in quality of life using QALYs derived from the EQ-5D. The data will also be linked to another parallel study in New Zealand where 126 patients with the same inclusion criteria have been treated in a similar trial; the form of analysis of the combined data has yet to be determined.

**Discussion:**

The morbidity and costs of non-cardiac chest pain are substantial and if a simple psychological treatment given by health professionals working in medical departments is beneficial it should prove to be of great value. Combining data with a similar study in New Zealand is an additional asset.

**Trial registration:**

ISRCTN14711101 (registered 05/03/2015)

## Background

Chest pain is one of the most common reasons for attending an Accident & Emergency Department. This is understandable as cardiac conditions often present with chest pain and many sufferers require emergency interventions to save life. However, only a minority of patients presenting with chest pain have a demonstrated physical cause for their conditions. The experience of chest pain, even if not related to cardiac pathology, is often alarming and frightening, and if inadequately managed, tends to reinforce rather than resolve the problems.

Atypical, better termed non-cardiac, chest pain, can have a number of underlying pathologies. Most importantly, it can be an indicator of genuine myocardial disease. A recent study of the outcome of 8762 patients attending rapid access chest pain clinics showed that of 599 patients who reached the primary end-point (ie died from coronary heart disease or had a myocardial infarction or had a hospital admission with unstable angina) after a mean of 2.6 years, 194 (32 %) had non-cardiac chest pain. However, this represented only 2.7 % of the population (6396 people) with non-cardiac chest pain whereas 16.5 % of those with angina reached the primary end-point [1]. Those with identifiable disease therefore only accounted for a minority of these. There is also an additional group of patients who already have had clear cardiac disease that has apparently been treated successfully but who continue to have persistent chest pain that cannot be explained cardiologically. Together, these constitute a psychosomatic majority, who often suffer greatly from their symptoms and attend repeatedly with their symptoms, only to be reassured that they have no active cardiac disease. Approximately 75 % of these patients satisfy the diagnosis for a mental state disorder, mainly panic disorder, depressive and other anxiety disorders [2]. These problems are not usually recognised as requiring mental health interventions by either the patients or their doctors, and, because these problems tend to be persistent, they tend to become repeat attenders at rapid access chest pain or cardiology clinics, often get admitted to hospital for further checks and tests, and yet very few develop significant cardiac pathology [3].

Cognitive behaviour therapy and related psychological treatments are normally effective in the treatment of anxiety and depressive disorders but have not shown quite such success in the treatment of non-cardiac chest pain. Kisely et al [4, 5] have carried out Cochrane systematic reviews and found 8 randomised trials, increasing to 10 in their updated review, but the benefits were relatively modest. They concluded that these trials ‘suggested a modest to moderate benefit for psychological interventions, particularly those using a cognitive-behavioural framework, which was largely restricted to the first three months after the intervention. The evidence for brief interventions was less clear. Further RCTs of psychological interventions with follow-up periods of at least 12 months are said to be needed [4]. In their later review they added that hypnotherapy might be useful [5].

Examination of the reasons for the relatively poor performance of psychological treatments for this condition suggest three factors handicap progress; (i) the resistance of patients to the notion of a psychological explanation for their condition, (ii) the confidence of the therapists in dealing with a condition that mimics major cardiac pathology, and (iii) the ability of therapists to deliver treatment well to such patients. Most well-trained CBT therapists are psychologists but they do not have the background knowledge of medicine that helps to reassure the patients with non-cardiac chest pain that they understand their ‘medical’ problems; conversely, cardiac support nurses are excellent in this latter understanding but not so skilled in the former [6]. In the proposed study we have trained general nurses to a high standard (using formal fidelity checks with an approved scale) for this adapted form of cognitive behaviour therapy for non-cardiac chest pain and feel that both of the above requirements are now being met.

A recent pilot study in this population [7] has also demonstrated greatly reduced usage of accident and emergency service contact and in-patient bed usage after CBT, and so we judge that there is a strong possibility that the treatment will more than pay for itself in cost savings. We think we have such a treatment, and so are conducting a randomised controlled trial comparing adapted cognitive behaviour therapy for such patients, delivered by a trained team within the clinic, with standard support and reassurance in the clinic (standard treatment) and to compare outcomes in terms of symptoms, social functioning, hospital and emergency department attendances and admissions, over a period of 12 months. Full details will be obtained of all health service costs as it is predicted that, if the active treatment is successful, patients will attend hospital less often and have fewer investigations, and this will more than offset the cost of the psychological treatment.

## Methods/design

The design is a two-arm parallel design randomized controlled trial carried out in three centres that compares a modified form of cognitive behaviour therapy for chest pain (CBT-CP) that also includes elements of a similar successful treatment for health anxiety (CBT-HA [8] that has been found to have lasting benefit in reducing symptoms, as well as showing superiority for nurse-delivered treatment [9].

The study has two major research questions:does an adapted form of cognitive behaviour therapy for non-cardiac chest pain given between 2 to 6 sessions, lead to reduced anxiety over health over 6 months and one year?does this adapted form of cognitive behaviour therapy reduce health service costs over a period of one year?

These hypotheses, together with related secondary ones, are being tested in a two-arm parallel randomised controlled trial of 2–6 sessions of cognitive behaviour therapy for chest pain (CBT-CP) or standard treatment (ST) in patients presenting with non-cardiac chest pain to cardiology settings who have presented at least once before in the previous year and do not have cardiac pathology of sufficient severity to explain the symptoms.

Our previous work has suggested that most of these patients can be treated successfully in a relatively short number of sessions with an adapted form of cognitive behaviour therapy (CBT), although a minority of handicapped patients may need more. The randomisation was carried out by an independent Clinical Trials Unit (Health Services Unit, CHaRT, University of Aberdeen with equal allocation to CBT and ST, with initial help given from Open-CDMS, a similar independent unit. Standard treatment (ST) will consist of normal management at the clinics concerned, consisting of investigative procedures to exclude pathology and feedback to patients about the findings.

Assessments of outcome include reduction in health anxiety recorded with the Health Anxiety Inventory [10] (primary outcome at 6 months), and Lucock Health Anxiety Questionnaire [11] adapted with agreement of the author for chest pain, self-completed analog ratings of both the frequency and severity of chest pain and discomfort developed with the aid of a patient (Inskip Scale), self-ratings of generalised anxiety and depression (using the HADS scale) [12], social functioning using the Social Functioning Questionnaire (SFQ) [13], The Schedule for Evaluating Persistent Symptoms (SEPS) [14, 15], that has been found in preliminary studies to be an accurate measure of medically unexplained symptoms, and quality of life using the EQ-5D scale [16] six months and one year (all secondary outcomes). In addition, all health service related costs will be recorded in the 6 months before randomisation and at 6 month intervals subsequently until one year and the costs for patients in the two arms of the trial compared.

### Target number of participants

From previous work with the Health Anxiety Inventory we calculated that a difference between the scores of 4 points is a clinically significant difference (but this is currently being reassessed as 2 may be a more appropriate value). Using data from a similar randomised controlled trial [17] we demonstrated a significant benefit between CBT and control with a sample of 49 patients. In this study with a standard deviation for the change of HAI at 1 year as 6.0 a sample size of 96 patients would be have 90 % power to demonstrate significance at the two-sided 5 % significance level. However, it is expected that a current very similar project in New Zealand under the supervision of RM, with HT as an applicant, will provide very similar data from at least a subset of their sample that will allow some form of combination of data, such as individual meta-analysis, that will add to the power of the study.

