### Status of the trial

Recruitment to the study began in July 2012 and the last patient was recruited in January 2015. No data have currently been examined. The CONSORT diagram illustrates the high numbers of people who present with potential non-cardiac chest pain (Fig. 1). 68 patients were recruited, a lower level than planned, but the revision in the clinically important difference (see above) makes the study only slightly underpowered.

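### The clinically important HAI difference is left open between 4 and 2 points after recruitment closed, yet the status section treats it as already revised

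*Protocol article*

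**What the plan says.** In the protocol article, Target number of participants, previous work is given as the reason that "a difference between the scores of 4 points is a clinically significant difference". The same sentence adds in parentheses: "but this is currently being reassessed as 2 may be a more appropriate value". That is present tense and undecided, and no evidence for 2 is given. The section then takes "a standard deviation for the change of HAI at 1 year as 6.0" and states that "a sample size of 96 patients would be have 90 % power to demonstrate significance" "at the two-sided 5 % significance level".

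Status of the trial reports that the last patient was recruited in January 2015, that 68 were recruited, and that no data had yet been examined. It accepts that this is below plan, but says that "the revision in the clinically important difference (see above) makes the study only slightly underpowered". It gives no number for the revised difference; the reference back can only be to the parenthesis above.

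The Analyses section compares mean HAI change from baseline to 6 months between arms. It uses no clinical threshold.

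**The concern.** The two sections disagree on the status of the value: pending in one, settled in the other. The document uses the value to justify the sample size and then to soften the shortfall. It is also the only yardstick the article offers a reader who wants to know whether an observed HAI difference matters to patients.

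If it stays open until results are known, a mean difference between 2 and 4 points could be called important or unimportant according to which value is picked. That choice would come after the shortfall and, if left long enough, after the data.

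**Working it through.** **Inputs.** Differences of 4 and 2 points, SD of change 6.0, two-sided 5%, 90% power and planned total 96 (Target number of participants); equal allocation (Methods/design); 68 recruited (Status of the trial).

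**Assumptions.** 34 per arm; the SD, given for 1 year, also holds at 6 months; no dropout; unadjusted comparison.

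**1. Which value the 96 rests on.** The article does not link the two explicitly, so I reproduced the figure.
- n per arm = 2 × (1.960 + 1.282)² × 6.0² / 4² = 47.3, rounded up to 48, so 96 in total. This matches the stated number; a t-based calculation gives 98.
- With 2 in place of 4, n per arm = 2 × (1.960 + 1.282)² × 6.0² / 2² = 189.1, rounded up to 190, so 380 in total.

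The planned 96 therefore rests on 4 points.

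**2. Precision with 68 patients.**
- SE = 6.0 × √(2/34) = 1.455.
- t(0.975, 66 df) = 1.997.
- 95% half-width = 1.997 × 1.455 = 2.91 points.

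**3. How often the two values would give opposite verdicts on the point estimate.** This is the probability that the observed difference falls from 2 up to 4, using the normal distribution with SE 1.455.

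| True difference | P(2 ≤ observed < 4) |
|---|---|
| 0 or 6 | 8% |
| 1 or 5 | 23% |
| 2 or 4 | 42% |
| 3 | 51% |

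For a true difference of 3, P(observed ≥ 2) = 0.754 and P(observed ≥ 4) = 0.246, so the probability is 0.508. This is the maximum, because 3 is the midpoint. If the result must also be significant (observed from 2.91 up to 4), the probability is about 28% at a true difference of 3 and 18% at a true difference of 2.

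**4. The status statement.** Power with 68 patients:

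| Difference | Normal approximation | t-based |
|---|---|---|
| 4 points | 78% | 77% |
| 2 points | 28% | 27% |

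Moving from 4 to 2 lowers power. The description of a slight deficit fits, at best, the 4-point value (about 78% against a planned 90%). It does not fit the revision that it cites.

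**The case against.** The strongest reply is that the article never says the primary result will be judged against 4 or 2. The value appears only in the sample size and status sections; the primary outcome and its analysis contain no such criterion, and rules for interpretation may sit in a full protocol or analysis plan that is not shown. This stands as far as the test goes: its validity and p-value do not depend on the choice. It does not remove the conflict, because the article itself calls the value clinically significant and then gives two incompatible accounts of its status.

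Second, no data had been examined, so the reassessment, though late, was made without knowledge of results. That also stands, and it is why the matter can still be settled cleanly. A reader might infer that the threshold was lowered because recruitment fell short. The documents do not show when or why the reassessment began; they show only that the status section uses it to mitigate the shortfall.

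Third, a reader might infer that 2 points is an empty benchmark because a significant result would always exceed it, so that only 4 can separate significance from importance. This does not hold. Read against the confidence interval, 2 does separate: an observed 3.5 has an interval of about 0.6 to 6.4, which is significant but does not exclude differences below 2. The article also foresees combining data with the New Zealand trial. If all 126 of its patients were added in equal arms with the same SD, the half-width would be 1.972 × 6.0 × √(2/97) = 1.70, and a significant estimate could then lie below 2.

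Last, preferring 4 is partly a judgement. The authors doubt it themselves, and the article shows no evidence for either value. That is a reason to allow a justified change, not to leave the value open.

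**Conclusion.** The point holds as a matter of interpretation and consistency. The article leaves the clinically important HAI difference at 4, possibly 2, and then relies on the revision as completed after recruitment closed at 68 of 96. The clinical reading of the primary difference and the status statement both rest on a value that is not fixed; the primary test does not. The conflict is between pending and done, not between two stated final numbers.

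The chance that the choice decides the verdict on the point estimate is up to about 51%, a worst case, and about 28% at the same true difference if significance is also required. These figures depend on the assumptions listed in the working. Baseline adjustment, which the Analyses section plans, could narrow the interval, and dropout would widen it; neither settles which value applies.

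**What to change.** While no data have been examined, state one value for the clinically important HAI difference, with its basis and the date it was fixed, and make the two sections agree. Unless evidence independent of the recruitment shortfall supports a change, keep the 4 points that reproduce the planned 96. In that case:

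- remove the reference to a revision from Status of the trial, and give the power of 68 patients for 4 points as it is (about 77 to 78% before dropout);
- report the primary estimate and its 95% confidence interval against 4;
- if 2 is shown as well, label it a post-recruitment value and do not rest the conclusion on it.

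The cost is wording in two sections and one interpretive sentence in the report. The downside is that a favourable clinical conclusion becomes somewhat harder to claim. If the trial team instead adopts 2 on independent evidence, the status section should say that 68 patients give only about 27 to 28% power for that difference.

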#### Ethics and consent

All patients recruited to the study are initially referred by clinical staff involved in their care and are then seen by a research assistant who gives each person a participant information sheet and explains the study. If, after getting appropriate answers to questions, patients agree to take part in the randomised study, they sign a declaration of informed consent. The study has been approved by the NRES (Ethical) Committee East Midlands, Northampton, UK (11/EM/0376).

#### Procedure

The patients seen are those satisfying the criteria below who presented with chest pain to either cardiology clinics and/or accident and emergency departments at three hospitals, King's Mill Hospital, Sutton-in-Ashfield, Nottinghamshire, the Hillingdon Hospital, Middlesex and the Royal Berkshire Hospital, Reading. Two other centres were included but the lack of a local principal investigator prevented recruitment. The procedures for the chest pain pathway are not the same at these three hospitals but are likely to be representative of the UK as in most hospitals there is no standard pathway for the assessment of non-cardiac chest pain.

#### Inclusions and exclusion criteria

The criteria for inclusion are (a) significant chest pain on at least two separate occasions in the past year in which no significant pathology explaining the symptoms was found, (b) signed consent to take part in the study, (c) age between 18 and 75. The exclusion criteria are (a) under active psychiatric care, (b) having received a prescription of a new psychoactive drug within the previous two months, (c) receiving, or on waiting list for, a formal psychological treatment. Those who are currently stable and on regular psychoactive medication (for more than 2 months) are eligible for the study.

#### Randomisation

Patients who are identified as eligible for the trial by cardiology and accident and emergency staff, and willing to take part, were first assessed by an independent research assistant. After baseline assessment all ratings and demographic details are recorded on a secure on-line data base, initially Open-CDMS in London and from 2014, CHaRT in the Health Services Research Unit, University of Aberdeen. Patients are then allocated to either CBT-CP or standard care in permuted stacked blocks (do we specify numbers) stratified by study centre. The allocated treatment is then passed to the trial coordinator (SC) who, if the patient is allocated to CBT-CP, informs the next available therapist at the centre concerned and then the patient, GP and consultant. Patients allocated to standard care are informed by letter or phone call and the GP and hospital team also notified. Follow up assessments are carried out by research assistants ignorant of original allocation after 6 and 12 months. All data are kept by CHaRT until the termination of the trial.

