#### Analyses

All analyses will be by intention to treat, analysed as randomised. The primary analysis will compare mean change scores of the Health Anxiety Inventory scale from the baseline to 6 months between the treatment and control groups. We shall conduct sensitivity analyses to examine data missing mechanism to decide whether imputation approaches are necessary. Random effects regression model will be used to estimate and test differences of mean change scores between the two comparison groups at 6 and 12 months simultaneously with adjustment for baseline score and key variables used for minimisation procedure. We shall also examine distribution of the outcome score. If a skewed distribution such as a Poisson one was shown, data transformation such as logarithmic transformation of raw data will be carried out before any statistical analysis.

Analyses of secondary outcomes will follow the same analytic procedure and statistical approaches. Economic analysis will follow a similar methodology except that wherever possible data will be analysed without transformation and using bootstrapping techniques for skewed data [18, 19].

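### CBT-CP patients are grouped by therapist and standard-care patients are not, but neither the sample size nor the listed model terms allow for this

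*Protocol article*

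**What the plan says.** Under Randomisation, a CBT-CP allocation goes to the trial coordinator, who "informs the next available therapist at the centre concerned". The Background describes the treatment as "delivered by a trained team within the clinic". Experimental interventions and Fidelity of treatment add that all therapists share one trainer and are each assessed and supervised with patients until they reach 75% of the maximum on an adapted rating scale. Standard care, in its own section, is the usual testing, explanation and reassurance; no trial therapist is involved.

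For the sample size, Target number of participants takes "a difference between the scores of 4 points is a clinically significant difference", a "standard deviation for the change of HAI at 1 year as 6.0", and concludes that "a sample size of 96 patients would be have 90 % power" at a two-sided 5% level. Methods/design sets the arms up "with equal allocation to CBT and ST". No design effect is mentioned.

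For the analysis, the Analyses section says: "Random effects regression model will be used to estimate and test differences of mean change scores between the two comparison groups". It fits both follow-up times together and lists baseline score and the allocation variables as adjustments. Therapist is not listed, and the level of the random effects is not named. Status of the trial reports 68 patients recruited and that the data had not yet been looked at.

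**The concern.** The design is partially nested. Patients who share a CBT-CP therapist may have correlated outcomes, while standard-care patients have no corresponding grouping. The Background makes such a correlation plausible: it names therapists' confidence, and their ability to deliver treatment well to these patients, among the reasons why earlier psychological treatments did relatively poorly.

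If outcomes do vary by therapist and the model ignores it, the variance of the CBT-CP mean is underestimated. The confidence interval for the treatment difference is then too narrow and the two-sided test rejects more than 5% of the time under the null. With few therapists, one unusually effective therapist could account for much of the observed difference, which would weaken any conclusion about nurse-delivered CBT-CP in general.

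**Working it through.** **Inputs from the article.** Difference 4 HAI points, SD of change 6.0, two-sided 5%, 90% power, 96 patients, 1:1 allocation (Target number of participants; Methods/design); 68 recruited (Status of the trial).

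**Inputs assumed.** 34 patients per arm; K = 3 to 6 therapists with equal caseloads; therapist ICC 0 to 0.10. The article gives none of these. Dropout is not stated and is not applied.

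**Step 1: reproduce the planned size.** Independent two-sample formula: n per arm = 2 × SD² × (1.960 + 1.282)² / difference² = 2 × 36 × 10.51 / 16 = 47.3, rounded up to 48, so 96 in total. The stated figure reproduces exactly, with no allowance for clustering.

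**Step 2: standard error under independence at the recruited size.** SE = 6.0 × √(2/34) = 1.455.

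**Step 3: add clustering in the CBT-CP arm only.** With m = 34/K patients per therapist:

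- design effect DE = 1 + (m − 1) × ICC
- true SE = 6.0 × √(DE/34 + 1/34)
- ratio R of true to independence SE = √((DE + 1)/2)
- actual type I error of the unadjusted test = 2 × (1 − Φ(1.96/R))
- power for 4 points with a correct SE = Φ(4/SE − 1.96)

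Example: K = 3, ICC 0.10. m = 11.3; DE = 1 + 10.33 × 0.10 = 2.033; R = √(3.033/2) = 1.232; SE = 1.792; type I error = 2 × (1 − Φ(1.591)) = 0.112.

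| K | m | ICC | DE | SE | R | Type I error | Power, 4 points |
|---|---|---|---|---|---|---|---|
| any | – | 0 | 1.000 | 1.455 | 1.000 | 0.050 | 78.5% |
| 6 | 5.7 | 0.02 | 1.093 | 1.489 | 1.023 | 0.055 | 76.6% |
| 6 | 5.7 | 0.05 | 1.233 | 1.538 | 1.057 | 0.064 | 73.9% |
| 6 | 5.7 | 0.10 | 1.467 | 1.616 | 1.111 | 0.078 | 69.7% |
| 3 | 11.3 | 0.02 | 1.207 | 1.529 | 1.050 | 0.062 | 74.4% |
| 3 | 11.3 | 0.05 | 1.517 | 1.632 | 1.122 | 0.081 | 68.8% |
| 3 | 11.3 | 0.10 | 2.033 | 1.792 | 1.232 | 0.112 | 60.7% |

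These figures use a normal critical value.

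**Step 4: what small-sample degrees of freedom cost.** Satterthwaite: df = (DE + 1)² / (DE²/(K − 1) + 1/33). CI width relative to the independence interval = R × t(df) / t(66), with t(66) = 1.997.

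- K = 3, ICC 0.02: df = 6.4, t = 2.41, width ratio 1.27.
- K = 3, ICC 0.10: df = 4.4, t = 2.68, width ratio 1.65.
- K = 6, ICC 0.02: df = 16.3, t = 2.12, width ratio 1.08.
- K = 6, ICC 0.10: df = 13.2, t = 2.16, width ratio 1.20.
- K = 3, ICC 0: df = 7.5, t = 2.33, width ratio 1.17. The penalty is paid even when there is no clustering.

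**The case against.** A reader might infer that the analysis treats all patients as independent and that its standard error is therefore likely to be too small. The article does not support either statement.

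On the first, the Analyses section specifies a random effects model and leaves the levels open. Fitting the two follow-up times together suggests a patient-level effect only, but that is an inference. This is a condensed article, and the random-effects structure is the kind of detail an analysis plan may settle.

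On the second, the ICC, therapist numbers and caseloads are all unknown. The 11% type I error needs the worst corner of the assumed range, three therapists with an ICC of 0.10; six therapists with an ICC of 0.05 give 6.4%, and an ICC of 0 gives no error at all. The same Background paragraph that blames therapist skill for earlier results also says that these nurses were trained to a high standard with fidelity checks, and Fidelity of treatment sets a common threshold. Both may reduce between-therapist variation.

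These objections stand against the stronger reading. They do not remove the point. The one-arm clustering is a feature of the design as described, and the sample size positively assumes independence. A fidelity threshold sets a floor and leaves room for differences above it. Adjusting for centre would not cure the problem either, because a common centre term cannot remove variation that exists in one arm only.

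**Conclusion.** The point holds in a limited form. The design is partially nested, the sample size makes no allowance for that, and no therapist effect is among the listed model terms. For any therapist ICC above 0, a model with only those terms understates the standard error of the 6-month HAI difference. The direction is certain under that condition; the size is not. For 3 to 6 therapists, about 34 CBT-CP patients and an ICC of 0 to 0.10, the true standard error is 0% to about 23% larger than the independence value, the type I error is 5% to about 11%, and power for 4 points is 78.5% down to about 61%. The article gives no basis for choosing a value within that range. This is a cheap improvement to the plan and does not show that the primary analysis is invalid.

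**What to change.** Keep the stated primary model. While the data are still unexamined, prespecify:

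1. A supportive partially nested analysis of the 6-month HAI: a random therapist effect in the CBT-CP arm only, standard-care patients entered as singletons, and small-sample degrees of freedom (Satterthwaite or Kenward-Roger).
2. A report of the number of therapists, their caseloads and the estimated therapist ICC.
3. The primary confidence interval recalculated under fixed ICCs of 0, 0.02, 0.05 and 0.10.

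Use the results to qualify how far the finding generalises across therapists. They should not be a gate on the primary conclusion: step 4 of the working shows that with three therapists the small-sample interval can be 27% to 65% wider than the independence interval, and 17% wider even at an ICC of 0.

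The cost is one extra model and one short table. They need the therapist's identity for each CBT-CP patient, which should be recoverable because the trial coordinator makes the therapist assignment. The drawback is that the therapist variance will be poorly estimated, or not estimable, with so few therapists, so the fixed-ICC intervals are the more informative display.
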